### 2.3. Interventions

The physical exercise intervention program was specifically designed for colorectal patients undergoing chemotherapy treatment. The training program was focused on resistance exercises, although daily aerobic exercises were also included. The intervention phase will last 12 weeks.

The study sample will be divided into two groups, the intervention group and the control group, detailed below.

#### 2.3.1. Intervention Group

The intervention group will perform a supervised resistance training program two days/week, combined with a physical activity promotion program to be carried out at home three days/week. All the supervised training sessions will be conducted by a physiotherapist in a healthcare center (Supplementary File S1, Comprehensive description of the intervention).

−Supervised training sessions: There will be two weekly sessions, each one lasting 50 min. Each session will have three distinct parts:
−Warm-up: 10 min of global strength and aerobic exercises at 60% of estimated VO_2_max, focusing on the areas to be primarily targeted during that session.−Resistance training: 6 resistance exercises targeting major muscle groups, with a duration of 30 min. Initial resistance will be set at 70% of the estimated 1-RM. When the participant is able to complete three sets of 12 repetitions at the set weight in two consecutive sessions, the weight will be increased by 10%. Sequenced resistance exercise followed in circuit training fashion with 30 s rest period between exercises and 90 s rest period between sets.−Cooldown/stretching: 10 min of a combination of breathing exercises and stretching.
The detailed description of each of the sessions is presented in the Supplementary Materials, which will be repeated in order and cyclically until the 12 weeks of training are completed.−Physical activity promotion: Participants will complete three weekly home training sessions that will not coincide with supervised training days. Each session will last 20 min, and they will complete two sets of five exercises, with one minute of work and one minute of rest.
−Day 1
Sitting and standing up from a chair.Lateral lunge.Supine bicycle.Elbow flexion with weights.Lateral shoulder raises.−Day 2
Lunge.Quadriceps wall isometric.Glute bridge.Frontal shoulder raises.Wall push-ups.−Day 3
Walking on tiptoes.Squats.Knee-to-chest raises.Abdominal crunch.Shoulder press with weights.

Additionally, all participants should walk for 60 min each day of the week.

#### 2.3.2. Control Group

The control group will only perform the physical activity promotion program 5 days/week. This will be combined with walking for 60 min every day of the week.

### 2.4. Outcomes

In the initial assessment, all variables, including sociodemographic factors, will be measured. Subsequently, all outcome variables will be assessed at the end of the 8-week intervention.

Personal and sociodemographic variables are as follows:Age (years)Sex (male or female)Weight (kilograms), height (meters) and body mass index (kg/m^2^)Time since diagnosis (years and months)Stage of the disease.Tumor location (colon or rectum).Type of chemotherapy and number of cycles.Radiotherapy (yes/no).

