#### 2.4.1. Primary Outcomes

The primary outcome measures are chemotherapy-induced peripheral neuropathy (CIPN). Self-reported neuropathy was evaluated using the European Organisation for the Research and Treatment of Cancer Quality of Life (EORTC QLQ) CIPN20 questionnaire, comprising 20 items categorized into three subscales that assess sensory, motor, and autonomic symptoms. Each item was rated on a Likert scale from 1 ‘not at all’ to 4 ‘very much’. Scores were then converted to a 0–100 scale, with higher scores indicating greater symptom severity.

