
### 2.5. Sample Size

The sample size calculation was performed using statistical software (G*Power 3.1). The calculation was carried out for a two-independent-group t-test. The effect size (d = 1.11) was estimated from the mean difference on the Chemotherapy-Induced Peripheral Neuropathy (CIPN) Trial Outcome Index (TOI) scale, obtained from Zimmer et al., 2017 [24], due to the similarity of interventions, and from the study by Balnd et al., 2019 [24], where the same scale (EORTC QLQ-CIPN 20) was used in the same group of patients but with a different intervention. A significance level of 0.05 and power of 95% were established. The estimated sample size was 38 subjects. Taking into account a 20% dropout rate based on the previous study [24], the required number of subjects was 44, with 22 subjects in each group.

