### 2.8. Statistical Methods

For the descriptive analysis of the data, normality will be checked with the Kolmogorov–Smirnov and Shapiro–Wilk tests (*n* < 30). Normally distributed variables will be defined by the mean, standard deviation, and value interval, while variables that do not follow a normal distribution will be defined by median and interquartile range. The qualitative variables of the study will be defined by frequencies and percentages.

Regarding quantitative analysis, a correlation analysis (Pearson’s correlation coefficient) will be used to demonstrate the validity of the assessment procedure selected in our study. Cronbach’s alpha coefficient will be used to demonstrate its reliability. For the comparison of two means, Student’s *t*-statistic inferential analysis (parametric test for independent samples), the Mann–Whitney U-statistic (non-parametric tests with two independent samples), and Wilcoxon’s *t*-test (non-parametric tests for repeated means) will be used. The comparison of three or more means has also been used and will be analyzed by means of an ANOVA test in the situation of independent groups (parametric via Snedecor’s F -ANOVA- and non-parametric via Kruskal–Wallis’ H). For repeated measures, Snedecor’s F test will be used in the parametric way and Friedman’s test in the non-parametric way. Correlations will be carried out by two methods: Pearson’s correlation (normal distribution) or Spearman’s correlation (non-normal distribution). Multivariate logistic regression analysis will be performed to determine the variables associated with events of interest. In the logistic regression model, variables that have been significant in the bivariate analysis or that are relevant to the study will be introduced into the logistic regression model. For qualitative or categorical variables, contingency tables and the Chi-Square test of significance will be used when there are two independent samples.

*p*-values of less than 0.05 will be considered significant, i.e., with a confidence interval of 95%. The statistical software IBM SPSS Statistics version 28.0.1 will be used.

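### CIPN20 is taken once after baseline, so the roughly 9 of 44 expected dropouts add nothing to the primary comparison; a mid-intervention form with a likelihood model would recover part of this

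*Protocol article*

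**What the plan says.** - **Schedule (section 2.4).** At the start, "In the initial assessment, all variables, including sociodemographic factors, will be measured". After that, "Subsequently, all outcome variables will be assessed at the end of the 8-week intervention". No other CIPN20 time point is given. Section 2.4.2 mentions two-monthly administration, but this concerns the QLQ-C30 and follows a sentence about another trial. It does not set a CIPN20 schedule here.
- **Duration.** Section 2.3 says "The intervention phase will last 12 weeks", and section 2.3.1 also works to 12 weeks. Section 2.4 speaks of 8 weeks.
- **Sample size (section 2.5).** "The calculation was carried out for a two-independent-group t-test", with d = 1.11, a 0.05 level and 95% power, giving 38. Then, "Taking into account a 20% dropout rate based on the previous study", 44 are to be randomised, 22 per arm.
- **Analysis (section 2.8).** Two means are compared by Student's t-test or Mann-Whitney U. A repeated-measures F test and Friedman's test are also named. No mixed model is named.

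**The concern.** A patient who leaves late has had weeks of chemotherapy and exercise, but without the end CIPN20 has no value in the two-group test. The repeated-measures F and Friedman tests, in their classical form, also drop incomplete cases.

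Symptom-related loss that differs by arm is plausible. Only the intervention arm meets a physiotherapist twice a week (section 2.3.1). Participants and evaluators know the allocation (section 2.7). Section 3.2 expects some loss through disease progression, and section 2.2 foresees early stopping of treatment for intolerance. Loss of this kind can be linked to neuropathy and so bias a completers-only comparison.

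An analysis plan could change the model, but it cannot recover a mid-course score that was never collected.

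**Working it through.** **1. The plan's own figures.** Inputs from section 2.5: d = 1.11, level 0.05, power 95%, equal arms. Exact noncentral-t power gives:
- one-sided: 19 per arm, 38 in all (power 95.6%), which matches the plan;
- two-sided: 23 per arm, 46 in all.

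So 38 is reproduced only as a one-sided test. For dropout, 38/(1 - 0.20) = 47.5, so 48. The planned 44 covers (44 - 38)/44 = 13.6% loss. These are side issues, but they show that there is no spare sample.

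**2. What 20% loss leaves.** 0.20 × 44 = 8.8 lost and 35.2 remain, or 17.6 per arm. Power at d = 1.11 is then about 94% one-sided or 89% two-sided. The standard error of the difference is √(2/17.6) = 0.337 SD. It is 0.337 × √(1 - 0.5²) = 0.292 SD after adjusting for a baseline score correlated 0.5 with the end score (an assumption).

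**3. Precision from a mid score.** Let n_c = 17.6 be the completers per arm and s the share of dropouts who filled in the mid form. Then n_m = 17.6 + 4.4s. Let r be the mid-end correlation, given baseline if baseline is adjusted for. The likelihood estimate has

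Var = σ²[(1 - r²)/n_c + r²/n_m], so the ratio to completers only is (1 - r²) + r² × n_c/n_m.

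The documents give neither r nor the timing of dropout, so both are assumed.

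| r | s | Variance ratio | Effective N | Power, 1-sided / 2-sided |
|---|---|---|---|---|
| any | 0 | 1.000 | 35.2 | 94.3% / 89.2% |
| 0.5 | 0.5 | 0.75 + 0.25 × 17.6/19.8 = 0.972 | 36.2 | 94.8% / 90.1% |
| 0.7 | 0.75 | 0.51 + 0.49 × 17.6/20.9 = 0.923 | 38.2 | 95.7% / 91.6% |
| 0.8 | 1 | 0.36 + 0.64 × 17.6/22 = 0.872 | 40.4 | 96.5% / 93.0% |

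Variance falls by about 3-13% and the standard error by about 1-7%, worth about 1 to 5 patients. All the gain comes from the dropouts. If the t-test is kept, the gain is zero.

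**4. Bias.** Large-sample simulation with unit-SD scores. Assumed: correlations of 0.5 for baseline-mid and baseline-end and 0.7-0.8 for mid-end; 20% loss in the control arm, more likely at higher symptom scores; any loss in the intervention arm random. These imply a mid-end correlation given baseline of (0.7 - 0.25)/0.75 = 0.60 to (0.8 - 0.25)/0.75 = 0.73, within the range of step 3. If loss depends on the mid score, the unadjusted completers-only bias is 0.16-0.18 SD.

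| Loss depends on | Baseline-adjusted completers | Likelihood with mid score, by share of dropouts captured |
|---|---|---|
| mid score | 0.11-0.13 SD | 100%: about 0; 75%: 0.02-0.03; 50%: 0.05-0.06; 25%: 0.08-0.09 |
| unseen end score | about 0.18 SD | 100%: 0.09-0.12; 50%: 0.13-0.15; 25%: up to 0.16 |

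The figures move by about 0.01 SD with the form of the dropout model. For scale, 0.11-0.13 SD is about 0.4 of the adjusted standard error (0.11/0.292 = 0.38; 0.13/0.292 = 0.45) and 10-12% of d = 1.11. If exercise helps, losing the worst-affected controls biases the estimate towards the null. The opposite pattern of loss would bias it away from the null.

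**The case against.** The strongest reply is that a baseline-and-end design over 8 or 12 weeks is a legitimate choice for 44 patients, that sections 2.4, 2.5 and 2.8 do not conflict on the number of assessments, and that the choice of estimator commonly belongs to an analysis plan that is not shown. This stands, and it is why the point is an improvement and not an error. It does not reach the schedule itself, which is stated.

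A reader might infer more than the documents support:
- **That one extra form keeps the whole 20% in.** It keeps in only those who leave after completing it, and nothing is said about when dropout occurs.
- **That bias disappears.** It does so only if every dropout supplied the mid score and loss depends on that score. Otherwise bias is reduced, not removed.
- **That the planned data cannot correct anything.** Baseline CIPN20 is already collected. Adjusting for it takes the bias from 0.16-0.18 to 0.11-0.13 SD, close to a third of it, with no new assessment.
- **That the form helps under the planned tests.** Under the t-test or Mann-Whitney U it adds nothing.

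Two practical objections also stand. The protocol gives no chemotherapy attendance schedule, and patients who stop treatment may not attend, so capture is uncertain. Section 2.2 also lists early stopping for intolerance as an exclusion. If that were applied after randomisation, it would remove such patients whatever they had completed. Seeking the end score from those who stop aims at the missing value directly and would recover more than a mid form. It complements the mid form and does not replace it.

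**Conclusion.** The point holds as a cheap improvement. With one post-baseline CIPN20 and tests that need the end score, about 9 of 44 patients would add nothing to the primary comparison at the plan's own dropout rate. The benefit of a mid score is mainly against bias, and the gain in precision is modest. The direction of the benefit is secure where some dropouts complete the form and a suitable model is used. Its size is not, because the correlations, the share captured and the dropout mechanism are all assumed.

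**What to change.** 1. Reconcile the 8-week duration in section 2.4 with the 12 weeks in sections 2.3 and 2.3.1.
2. Add one self-completed CIPN20 in both arms at mid-intervention. Keep the end of intervention as the primary time point.
3. Seek the end CIPN20 from patients who stop the programme or chemotherapy, and state whether the intolerance exclusion in section 2.2 can apply after randomisation.
4. Estimate the end-of-intervention contrast with a likelihood repeated-measures model (arm, visit, arm-by-visit, baseline CIPN20, baseline-by-visit) that includes every randomised patient with any post-baseline score.

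The cost is one more 20-item form per patient, contact with those who stop, a line in the schedule and wording for the analysis. No extra patients are needed. The downside is a slight burden and one more unblinded self-report score.

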#### 2.4.1. Primary Outcomes

The primary outcome measures are chemotherapy-induced peripheral neuropathy (CIPN). Self-reported neuropathy was evaluated using the European Organisation for the Research and Treatment of Cancer Quality of Life (EORTC QLQ) CIPN20 questionnaire, comprising 20 items categorized into three subscales that assess sensory, motor, and autonomic symptoms. Each item was rated on a Likert scale from 1 ‘not at all’ to 4 ‘very much’. Scores were then converted to a 0–100 scale, with higher scores indicating greater symptom severity.


### 2.5. Sample Size

The sample size calculation was performed using statistical software (G*Power 3.1). The calculation was carried out for a two-independent-group t-test. The effect size (d = 1.11) was estimated from the mean difference on the Chemotherapy-Induced Peripheral Neuropathy (CIPN) Trial Outcome Index (TOI) scale, obtained from Zimmer et al., 2017 [24], due to the similarity of interventions, and from the study by Balnd et al., 2019 [24], where the same scale (EORTC QLQ-CIPN 20) was used in the same group of patients but with a different intervention. A significance level of 0.05 and power of 95% were established. The estimated sample size was 38 subjects. Taking into account a 20% dropout rate based on the previous study [24], the required number of subjects was 44, with 22 subjects in each group.

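### Section 2.5 claims 95% power from 38 subjects, but under the most natural, two-sided reading of section 2.8 the power is about 91%

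*Protocol article*

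**What the plan says.** Section 2.5 of the protocol article prints nearly every input of the calculation. The software is G*Power 3.1. The test is named: "The calculation was carried out for a two-independent-group t-test". The effect size is given: "The effect size (d = 1.11) was estimated from the mean difference". The error rates and the result follow: "A significance level of 0.05 and power of 95% were established. The estimated sample size was 38 subjects". After a dropout allowance of 20%, "the required number of subjects was 44, with 22 subjects in each group". The one setting not given is the number of tails.

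Section 2.8 describes the analysis. Two means are compared by Student's t, "inferential analysis (parametric test for independent samples"), or by the Mann–Whitney test where the parametric test does not apply. The significance rule is that p-"values of less than 0.05 will be considered significant, i.e., with a confidence interval of 95"%. No section declares a one-sided test.

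**The concern.** A p-value threshold of 0.05 matched to a 95% confidence interval is the ordinary two-sided 5% rule; a one-sided test at 0.05 corresponds to a 90% two-sided interval. The sample size should therefore come from a two-sided calculation, and with the printed inputs that calculation does not return 38.

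Two things are at stake. First, the published power would not be a property of the planned primary comparison. Second, with the tails unstated, the choice between a one-sided and a two-sided primary test stays open until the data are seen. That choice doubles the error rate in the favourable direction, from 2.5% to 5%.

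**Working it through.** **Inputs.** All are from section 2.5: d = 1.11, alpha = 0.05, target power 95%, two independent groups, 38 evaluable, 44 randomised 1:1, 20% dropout. The two-sided reading is inferred from section 2.8.

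**Method.** Exact power of the two-sample t-test from the noncentral t distribution:

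- degrees of freedom: df = n1 + n2 − 2
- noncentrality: δ = d × √[n1·n2/(n1 + n2)], which is d × √(n/2) for equal groups
- one-sided power: P(T > t(0.95, df)), with T noncentral t (df, δ)
- two-sided power: P(T > t(0.975, df)) + P(T < −t(0.975, df)); the second term is negligible here

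**Step 1: reproduce the plan's figure.** One-sided at 0.05:

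- 18 per group: δ = 1.11 × √9 = 3.33, df = 34, critical value 1.691, power 94.7%
- 19 per group: δ = 1.11 × √9.5 = 3.421, df = 36, critical value 1.688, power 95.6%

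The smallest equal-group size reaching 95% is 19 per group, or 38, exactly as stated.

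**Step 2: the same inputs, two-sided at 0.05.**

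| Evaluable per group | Total | δ | Critical value | Power |
|---|---|---|---|---|
| 18 | 36 | 3.330 | 2.032 | 89.9% |
| 19 | 38 | 3.421 | 2.028 | 91.4% |
| 22 | 44 | 3.682 | 2.018 | 94.9% |
| 23 | 46 | 3.764 | 2.015 | 95.7% |

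At 38 the shortfall is 95 − 91.4 = 3.6 points, and the type II error is 100 − 91.4 = 8.6%. Equal groups need 46 to reach 95%.

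**Step 3: other explanations for 38.**

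- *Rounding of d.* For d between 1.105 and 1.115, two-sided power at 38 runs from 91.2% to 91.7%, and the requirement for 95% is 44 to 46. Rounding does not produce 38.
- *Normal approximation.* Two-sided at 95% power it gives 22 per group (44); one-sided it gives 18 per group (36). Neither is 38.
- *A different power.* Two-sided at 90% power, 18 per group falls just short (89.9%) and 19 per group suffices (91.4%). So 38 is also the two-sided answer for 90% power.

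The printed 38 therefore fits two histories: a one-tailed calculation at 95%, or a two-tailed calculation at 90% with the power misreported.

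**Step 4: power after the plan's own dropout.** 44 × 0.80 = 35.2, so about 35 completers. Split 17 and 18: δ = 1.11 × √(17 × 18/35) = 3.282, df = 33, critical value 2.035, two-sided power 89.0%.

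**The case against.** The strongest reply is that nothing printed is contradicted. Section 2.5 gives no tails, and section 2.8 does not contain the term two-sided. The confidence-interval phrase is a loose gloss at the end of a general list of procedures that singles out no primary test. The summary and abstract speak of reducing neuropathy, which is directional, and a one-tailed calculation fits section 2.5 exactly. A condensed article may also leave the number of tails to the full protocol.

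Part of this stands: the two-sided reading is an inference. It is still the more natural one. A 95% interval paired with p below 0.05 points to it, the main objective in the Introduction is worded neutrally as evaluating efficacy, and no one-sided test is declared. If one-sided was intended, 38 is right for section 2.5, but section 2.8 then needs correcting. Nor is this only an omitted detail: the article prints inputs, result and decision rule, and together they do not agree.

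A reader might infer two stronger things that the article does not support:

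- **That a one-tailed G*Power setting was used.** Step 3 shows that a misreported power explains 38 equally well.
- **That the trial is badly underpowered or must enrol more.** If d = 1.11 holds, power stays near 90%. The 94.9% at 44 evaluable is within rounding of d (95.1% at d = 1.115), so that figure alone should carry little weight.

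**Conclusion.** The stated 95% power does not hold under the most natural reading of the article's own significance rule. Two-sided power with 38 evaluable is 91.4%, which is 3.6 points lower, and about 89% if 20% of the 44 are lost. The arithmetic is secure. The conclusion rests on three assumptions: that section 2.8 means a two-sided 5% test, that the primary comparison is the t-test used for the sample size, and that d = 1.11 is taken as given. Whether the tail setting or the reported power is the slip cannot be settled from the article.

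This is a correction to a stated figure with moderate practical impact. It does not overturn the design.

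**What to change.** In section 2.5, state that the primary test is two-sided at 0.05, and replace the 95% with the power this gives. Suggested wording: with 38 evaluable participants (19 per group), a two-sided independent-groups t-test at the 0.05 level has about 91% power for d = 1.11; if 20% of the 44 randomised are lost, leaving about 35, power is about 89%. Giving both figures matters, because 38 evaluable is more than the plan's own dropout rate would leave.

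If the full protocol did intend a one-sided test, that should be declared and section 2.8 brought into line, before results are known.

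The cost is a sentence or two and a slightly less favourable power figure. No participants are added, and the conduct of the trial does not change.

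### 44 randomised covers 13.6% loss from 38 evaluable, not the stated 20%; after 20% loss the stated 95% power is missed on either sidedness, by about 1 point one-sided or 6 two-sided

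*Protocol article*

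**What the plan says.** Section 2.5 (Sample Size) gives the whole chain. The design basis is "The calculation was carried out for a two-independent-group t-test", run in G*Power. For the effect, "The effect size (d = 1.11) was estimated from the mean difference" reported on a neuropathy scale in earlier work. For the error rates, "A significance level of 0.05 and power of 95% were established". The result is "The estimated sample size was 38 subjects". The dropout step then reads "Taking into account a 20% dropout rate based on the previous study [24], the required number of subjects was 44", split as 22 per group. The figure of 44 also appears in the Simple Summary and the Abstract.

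Section 2.5 does not say whether the test is one- or two-sided. Section 2.8 (Statistical Methods) says that p-"values of less than 0.05 will be considered significant, i.e., with a confidence interval of 95"%. It names no one-sided test.

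**The concern.** The figures 38, 20% and 44 stand within two consecutive sentences, and the last does not follow from the first two. A required number of evaluable subjects N with expected loss L is protected by randomising N/(1 − L). Here that gives a number above 44, and so does the cruder habit of multiplying by 1 + L.

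At stake is the claim that 44 randomised still gives 95% power after the loss that the plan itself expects. Section 3.2 names disease progression as a reason why subjects may be lost, so dropout is a realistic prospect here. If the trial ends with about 35 evaluable and a null result, readers would judge that result against a power that the design does not have.

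**Working it through.** **Inputs.** All are from section 2.5 unless noted: two-independent-group t-test; d = 1.11; alpha 0.05; target power 95%; 38 subjects before dropout; 20% dropout; 44 randomised, 22 per group. Sidedness is not stated there; section 2.8 implies two-sided.

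**Step 1: reproduce the 38.** Exact power uses the noncentral t distribution with n1 + n2 − 2 degrees of freedom and noncentrality d × √(n1·n2/(n1 + n2)). For 19 + 19 the noncentrality is 1.11 × √9.5 = 3.42.
- One-sided 5%: the smallest equal groups that reach 95% are 19 each, 38 in total, with power 95.6%. This reproduces the plan's figure.
- Two-sided 5%: 95% needs 23 each, 46 in total, with power 95.7%. At 38 the power is 91.5%.

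So 38 is a one-sided number.

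**Step 2: inflate 38 for 20% dropout.**
- Correct formula: 38/(1 − 0.20) = 47.5, so 48 (24 per group).
- Common shortcut: 38 × 1.2 = 45.6, so 46.
- What 44 allows: (44 − 38)/44 = 6/44 = 13.6% of those randomised, or 6/38 = 15.8% if expressed on the base of 38.

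None of these links 38, 20% and 44.

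**Step 3: apply 20% loss to 44.** 44 × 0.80 = 35.2, so about 35 evaluable, 3 fewer than 38. For 17 + 18 the noncentrality is 1.11 × √(306/35) = 3.28.

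| Evaluable | Loss from 44 | Power, one-sided 5% | Power, two-sided 5% |
|---|---|---|---|
| 22 + 22 = 44 | 0% | 97.6% | 94.9% |
| 19 + 19 = 38 | 13.6% | 95.6% | 91.5% |
| 18 + 18 = 36 | 18.2% | 94.7% | 89.9% |
| 17 + 18 = 35 | 20.5% | 94.2% | 89.0% |

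The exact 35.2 lies between the last two rows, so rounding in the plan's favour, to 36, does not restore 95% on either basis.

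**Step 4: separate the two sources of the shortfall.**
- Inflation error (38 down to 35 evaluable): 95.65 − 94.17 = about 1.5 points one-sided; 91.45 − 88.98 = about 2.5 points two-sided.
- Sidedness, at the full 38: 95.65 − 91.45 = 4.2 points, present before any shortfall in evaluable subjects.

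As a check on this split, randomising the correctly inflated 48 leaves 48 × 0.80 = 38.4, about 38 evaluable, and two-sided power is still only 91.5%.

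**The case against.** The best defence is that little is lost. On the one-sided basis that reproduces 38, power after 20% loss is 94.2%, less than one point below target. The shortfall is about 3 evaluable participants. The slip changes no endpoint, test, allocation or alpha, and it cannot bias the estimate. The shortcut result of 46 is also only two above 44. Most of this stands, and it limits the severity. It does not rescue the sentence: 46 comes from the wrong formula and is still not 44, and 95% is missed on both bases. Nor is this a detail left to a fuller document, because the article states the figures.

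A reader might infer something stronger: that the dropout error itself takes power from 95% to 89%. The documents do not support that. The 89% combines two things, and the larger is that 38 is a one-sided figure being used for what looks like a two-sided analysis. The two-sided reading is itself an inference from the pairing of p < 0.05 with a 95% interval in section 2.8. It is a reasonable inference, but section 2.5 does not state it.

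**Conclusion.** The dropout sentence in section 2.5 is wrong as written. From 38 evaluable, a 20% allowance gives 48, not 44; the 44 protects against 13.6% loss, and at 20% about 35 remain. Power is then 94.2% one-sided or 89.0% two-sided, against the stated 95%. The part due to the inflation error is about 1.5 points one-sided or 2.5 points two-sided. The remaining distance to 89% belongs to the unstated sidedness.

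These figures rest on the plan's own d = 1.11 and alpha 0.05, on loss spread about evenly over the two groups (17 and 18), and on the t-test named in section 2.5. They say nothing about whether d = 1.11 is plausible. It would go too far to conclude that the trial is seriously underpowered at its own effect size or that recruitment must rise. This is a moderate reporting correction.

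**What to change.** Reword section 2.5, with every figure on one stated sidedness.

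1. State whether the calculation is one- or two-sided. Two-sided agrees with section 2.8; if one-sided is meant, section 2.8 must be brought into line.
2. Remove the claim that 44 already includes a 20% allowance.
3. Replace it with power at the fixed size. On the two-sided basis, for example:

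> With 44 randomised and a two-sided 5% t-test at d = 1.11, power is 94.9% with no dropout, 91.5% with 38 evaluable (13.6% loss) and about 89% with 35 evaluable (20% loss).

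The sentence that gives 38 for 95% power must change at the same time. Otherwise a one-sided 38 would stand beside a two-sided 89%. If one-sided is chosen, the matching figures are 97.6%, 95.6% and 94.2%.

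The cost is wording only, with no added recruitment. The downside is that the stated power becomes less favourable. For reference, if the sponsor preferred to keep 95% power after 20% loss at d = 1.11, the numbers to randomise would be 48 one-sided, or 46/0.80 = 57.5, so 58, two-sided.
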